#### Process for recording adverse events

All adverse events will be recorded by researchers when they are made aware of the event by the patient, carer, the treating clinicians, or therapists. Adverse event reporting information will be included in the training given to the therapy teams delivering the intervention and they will be given copies of the adverse event reporting forms (Additional file 3) and details of how to return them to the research team. Details of the adverse event reporting procedure will also be included in letters to the participants’ GP and consultant informing them of their participation in the study. The adverse event form will have two sections, the first is for the healthcare professional to complete and return to the study manager. The study manager will liaise with the chief investigator who will determine whether the adverse event is serious or not and whether it is related to the study. The chief investigator will complete the second part of the form. All serious adverse events, along with the chief investigator’s assessment of whether it is related to the study, will be sent to the Data Monitoring and Ethics Committee (DMEC) for a second opinion. The trial study manager will record the information on the study master file and inform the clinical trials unit manager. Study-related serious adverse events will be reported to the sponsor and to the academic school (Schools of Medical and Healthcare Sciences, College of Health and Behavioural Science) within 24 h of being determined as serious. They will also be reported to the DMEC chair and the research ethics committee.

#### Referral of vulnerable adults to protection agencies (protection of vulnerable adults referral)

Staff and researchers recruiting patients have been provided with statutory protection of vulnerable adults (POVA) training by the BCUHB within vulnerable adult protection framework [50] in accordance with Welsh Government guidance [51,52]. A mechanism of immediate risk assessment and onward referral to appropriate local authorities, police and BCUHB POVA hub has been developed within the framework of the Human Rights Act 1998 [53] and Data Protection Act 1998 [54] if abuse or neglect is suspected, observed or disclosed by the participants.

#### Statistics

##### Sample size

We estimate that we will recruit 25% of eligible patients with a proximal femoral fracture admitted to the three acute hospitals in BCUHB and randomise them to either the enhanced rehabilitation programme or usual care. In order to estimate the standard deviation of the primary outcome measure (Barthel index), which will be used in a power calculation for a future definitive RCT, with a high level of confidence a sample size of at least 50 participants completing the trial is advisable [55].

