### Cohort study

#### Selection of subjects for cohort study

The cohort will consist of an anonymised data set of all patients 65 years of age and over admitted to the three main acute hospitals of Betsi Cadwaladr University Health Board (BCUHB) in North Wales (Wrexham Maelor, Ysbyty Glan Clwyd and Ysbyty Gwynedd) with hip fracture during the first 6 months of the study period; who will subsequently be followed up for 3 months. BCUHB is the largest health board in Wales with a population of 692,000. Data collected will include type of fracture, type of surgery, length of stay in acute hospital, serious complications, mortality rates, repeat fractures, place of residence on admission, place of discharge from acute and community hospitals and serious illnesses requiring hospital re-admission. Audit figures returned to the National Hip Fracture Database give a conservative estimate that approximately 100 to 180 patients are admitted to each of these hospitals (a total of 300 to 540) in a 6-month period [19].

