### Randomised feasibility study

#### Selection of subjects for randomised feasibility study

Of all those admitted, we anticipate that we will be able to identify and invite 150 patients (50% of a conservative estimate of the total) from the three hospital sites across BCUHB during the 6-month study period to participate in the embedded feasibility study comparing usual care with the enhanced rehabilitation package using a randomised design. We will attempt to recruit 50 patients to this randomised feasibility study. The number of eligible patients, the recruitment and retention rates and the number who completed the outcome questionnaires will be recorded. It will be important to determine whether random allocation to either intervention arm is acceptable to patients, carers and clinicians providing the service. The feasibility study will also be an opportunity to test a package of process and outcome measures, including economic measures, for the main trial and to inform the effect size for a future sample size calculation. These patients will also be recruited to a triangulation study which aims to compare the quality of data collected about service use from patient-reported outcome measures compared with extracting the same information from patient electronic records.

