#### Withdrawal of participants

Participant withdrawal from the study will not affect their medical or social care, and this point will be emphasised in the patient information sheet and during the informed consent process. Similarly, withdrawal of carer participants will not affect the medical or social care of the hip fracture patient they are caring for.

Non-completion of the follow-up questionnaires or physical function tests will not constitute formal withdrawal from the trial, and unless the participant requests withdrawal of their data completely, it may be used to impute values for the analysis. The imputation of missing values will ensure that the dataset is utilised to its full power.

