#### Statistical analysis

The main outcomes of the feasibility study will be the descriptive statistics of recruitment and retention figures as follows:The number of patients screened for eligibility;The number of eligible patients and a comparison with the numbers in the cohort data set. A full trial will be considered feasible if 50% of the patients identified in the cohort study are eligible for inclusion in the trial. Using the lower end of a 95% confidence interval, this gives a minimum of 44% required to be eligible;Number of ineligible patients and frequency of predetermined reasons for ineligibility (lack of mental capacity to consent, not living independently, living outside the study area, age, did not have surgery for their hip fracture, living within the study area but outside the area where the intervention could be delivered, other);The number of eligible patients recruited (and so by implication were willing to be randomised) will be expressed as a percentage of the numbers in the cohort data set and as a percentage of the numbers identified as eligible in the feasibility study. The full trial will be considered feasible if the expected 25% of eligible patients are recruited to the trial, using the 95% confidence interval this gives a minimum of 18% recruitment;The number of eligible patients not recruited and the frequencies and reasons for this (e.g. burden, did not want to be in a research study);The number who withdraw after baseline assessment and randomisation and the reasons for withdrawal; andThe number who completed the various outcome measurements at baseline and at 3-month follow-up. The researchers who administer the outcome measures will record the reasons for any non-completion. The retention rate for the full trial to be feasible is 75%, again using a 95% confidence interval, this gives a minimum of 63% retention for the full RCT to be plausible.

The following demographics descriptors will be presented overall and per randomised group:Date of birth (age)GenderType of fractureMarital status and living arrangementsPlace of residence prior to admissionPlace of discharge from acute or community hospitalAbbreviated mental test score (AMTS)

All outcome measures will be presented descriptively at all of the time points that they have been collected.

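### The sample size rests on 50 participants completing, but the plan recruits 50 and works with 75% retention, so about 38 would complete

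*Protocol article*

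**What the plan says.** The protocol article gives one reason for the size of the randomised study. The Sample size section wants the SD of the Barthel index for a later power calculation, and for that purpose "a sample size of at least 50 participants completing the trial is advisable". It cites an outside source for this number and states no numerical precision.

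The section on selecting subjects for the randomised feasibility study sets the target: "We will attempt to recruit 50 patients to this randomised feasibility study". It draws these patients from a 6-month pool: "we anticipate that we will be able to identify and invite 150 patients (50% of a conservative estimate of the total").

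Three rates go with these numbers:
- Eligibility (Statistical analysis): "A full trial will be considered feasible if 50% of the patients identified in the cohort study are eligible for inclusion in the trial", with a minimum of 44%.
- Recruitment (Sample size): "We estimate that we will recruit 25% of eligible patients", with a minimum of 18% under Statistical analysis.
- Retention (Statistical analysis): "The retention rate for the full trial to be feasible is 75" per cent, with a minimum of 63%. The Discussion repeats the threshold.

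The section on expected duration gives a recruitment period of 9 months, not 6. The cohort section puts admissions at "approximately 100 to 180 patients are admitted to each of these hospitals (a total of 300 to 540) in a 6-month period". The section on withdrawal of participants adds: "The imputation of missing values will ensure that the dataset is utilised to its full power".

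**The concern.** The same number, 50, serves as the count who must finish and as the count to be recruited. The two agree only if nobody is lost. The patients are aged 65 or over and have recently had a hip fracture, follow-up stops if capacity is lost, and the plan itself treats 75% retention as acceptable.

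The SD is the sole stated basis for the size and is meant to feed the sample size of the definitive trial. An SD from fewer completers is less certain, and a definitive trial planned on a point estimate that happens to be low would be too small. A reader should be able to see how many completers the plan expects and how well they will fix the SD.

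The sentence on imputation could suggest that missing 3-month outcomes cost nothing. For estimating an SD that is not so: filled-in values cannot stand in for the same number of observed ones.

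**Working it through.** **1. Which denominators the plan used.** The lower limit is p − 1.96 × √(p(1 − p)/n).
- Eligibility, p = 0.50, n = 300: 44.3% (stated 44%).
- Recruitment, p = 0.25, n = 150: 18.1% (stated 18%).
- Retention, p = 0.75, n = 50: 63.0% (stated 63%).

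All three reproduce. For retention, any n from 47 to 54 rounds to 63%. With 67 randomised the limit would be 64.6%, and with 38 it would be 61.2%. The retention limit therefore fits about 50 *randomised*, in line with the recruitment target.

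**2. Completers from the stated target.**
- 50 × 0.75 = 37.5, about 38.
- 50 × 0.63 = 31.5, about 32.
- For 50 completers at 75% retention: 50 / 0.75 = 66.7, so 67 randomised.

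**3. Recruits and completers from the accrual figures.** Recruits = admissions × 0.50 × 0.25; completers = recruits × 0.75. The 9-month rows assume that the 6-month admission rate continues and that recruitment does not stop at 50.

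| Admissions per 6 months | Window | Eligible | Recruits | Completers |
|---|---|---|---|---|
| 300 | 6 months | 150 | 37.5 | 28.1 |
| 300 | 9 months | 225 | 56.3 | 42.2 |
| 540 | 6 months | 270 | 67.5 | 50.6 |
| 540 | 9 months | 405 | 101.3 | 75.9 |

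Reaching 50 recruits from 150 invited needs 50 / 150 = 33%, not 25%. Over 9 months the conservative base passes 50 recruits at 25%, so this mismatch comes from the two recruitment periods.

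**4. What this does to the SD.** The 95% limits, as multiples of the estimate, are √(df/χ²) at the 97.5th and 2.5th percentiles. With the SD pooled over two arms, df = n − 2. Approximate normality is assumed.

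| Completers | 95% limits for the SD | Upper limit squared (variance) |
|---|---|---|
| 50 | 0.83 to 1.25 | 1.56 |
| 42 | 0.82 to 1.28 | 1.64 |
| 38 | 0.81 to 1.30 | 1.69 |
| 28 | 0.79 to 1.37 | 1.88 |

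For a fixed target difference the required size of a later trial is proportional to the variance. The last column is therefore the factor by which that trial could need to be larger than the point estimate suggests.

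**The case against.** **Admissions may be higher.** The plan gives 300 to 540 per 6 months and does not say that recruitment stops at 50. At the upper figure the same rates give about 51 completers in 6 months and 76 in 9. This stands. A reader might infer that the plan cannot produce 50 completers, or that 28 to 42 is its forecast, and the documents support neither. The 28 belongs only to the conservative 6-month base. But the stated target is 50 recruits, and a target of 50 does not give 50 completers.

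**75% is a threshold, not a forecast.** True, and the Discussion asks for more than 75%. It is still the only retention figure offered, and any retention below 100% leaves fewer than 50.

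**The number is only advisable, and no precision is promised.** Also true. A reader might say that the plan fails to deliver a stated precision, but it states none beyond a high level of confidence. What fails is the match between the justification and the target.

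**Imputation is a matter for the analysis plan.** The choice of method is. The protocol names none and does not say that imputed values enter the SD. A reader might infer that the SD will be biased downwards. That would follow from filling in arm means, which the plan never proposes. Multiple imputation using the baseline score could recover some information. Observed values are not free of bias either, because participants who lose capacity are not followed up. What remains is narrower: the claim about power should not be read as making up for missing completers.

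**Conclusion.** The point holds. The plan justifies its size by at least 50 participants completing, sets 50 as the number to recruit, and allows nothing for attrition. At its own 75% retention about 38 complete, and about 32 at the 63% limit. This part does not depend on admissions; it assumes only that recruitment ends at 50 and that retention is near the plan's threshold.

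Separately, 150 invited in 6 months at 25% gives about 38 recruits, not 50. The same base over 9 months gives about 56, so the two recruitment periods have to be reconciled before the target can be checked.

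The statistical cost is modest. With 38 completers instead of 50, the upper 95% limit for the SD moves from 1.25 to 1.30 times the estimate, and the corresponding variance factor from 1.56 to 1.69.

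**What to change.** - **Sample size and selection sections.** Use the same statement in both, for example: *50 randomised, about 38 expected to complete at 75% retention; the 95% interval for the pooled Barthel SD is then about 0.81 to 1.30 times the estimate (0.83 to 1.25 with 50 completers).*
- **Recruitment period.** Say whether recruitment to the randomised study lasts 6 or 9 months, and give the number to be invited over that same period. On the conservative base this is 150 for 6 months or 225 for 9.
- **Withdrawal section.** Remove the statement that imputation secures full power, at least as a support for the SD. Report the SD from observed 3-month Barthel values with its confidence interval, note that it describes those followed up, and use that interval, not the point estimate alone, when planning the definitive trial.

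All this is wording. It needs no extra patients, and the stated precision becomes slightly less favourable.

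If the sponsor prefers to keep 50 *completing*, the target becomes 67 randomised. At the plan's rates that is about 267 eligible patients (66.7 / 0.25) and 533 admissions (66.7 / 0.25 / 0.50). This is near the top of the stated 6-month range, or about 356 admissions per 6 months (533 / 1.5) over 9 months. The text would then have to show that accrual supports it.

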#### Statistical analysis

The main outcomes of the feasibility study will be the descriptive statistics of recruitment and retention figures as follows:The number of patients screened for eligibility;The number of eligible patients and a comparison with the numbers in the cohort data set. A full trial will be considered feasible if 50% of the patients identified in the cohort study are eligible for inclusion in the trial. Using the lower end of a 95% confidence interval, this gives a minimum of 44% required to be eligible;Number of ineligible patients and frequency of predetermined reasons for ineligibility (lack of mental capacity to consent, not living independently, living outside the study area, age, did not have surgery for their hip fracture, living within the study area but outside the area where the intervention could be delivered, other);The number of eligible patients recruited (and so by implication were willing to be randomised) will be expressed as a percentage of the numbers in the cohort data set and as a percentage of the numbers identified as eligible in the feasibility study. The full trial will be considered feasible if the expected 25% of eligible patients are recruited to the trial, using the 95% confidence interval this gives a minimum of 18% recruitment;The number of eligible patients not recruited and the frequencies and reasons for this (e.g. burden, did not want to be in a research study);The number who withdraw after baseline assessment and randomisation and the reasons for withdrawal; andThe number who completed the various outcome measurements at baseline and at 3-month follow-up. The researchers who administer the outcome measures will record the reasons for any non-completion. The retention rate for the full trial to be feasible is 75%, again using a 95% confidence interval, this gives a minimum of 63% retention for the full RCT to be plausible.

The following demographics descriptors will be presented overall and per randomised group:Date of birth (age)GenderType of fractureMarital status and living arrangementsPlace of residence prior to admissionPlace of discharge from acute or community hospitalAbbreviated mental test score (AMTS)

All outcome measures will be presented descriptively at all of the time points that they have been collected.

An exploratory correlation analysis will be performed. Correlations will be calculated using Pearson’s product moment correlation coefficient for specific pairs of variables as outlined below. All of the correlations will be completed at both baseline and 3-month follow-up.Barthel index versus 8-ft get-up-and-go test.

This is exploring the relationship between the patient’s current functional status and the physical function test used to assess their agility and dynamic balance.Barthel index versus general self-efficacy scale/falls efficacy scale-international/self-efficacy for exercise scale.

There are three different self-efficacy measures that are being used within the feasibility stage of this study. All three of these will be correlated with the primary outcome measure to evaluate any differences between them and assist in the decision as to which measure to take forward to a full trial. The correlation is aiming to compare the patient’s self-efficacy with their current functional status to see if a link is present.

Preliminary exploratory analysis of the primary outcome measure (Barthel index) will be completed to find estimates of the means, standard deviations and confidence intervals for both of the treatment arms. These values will also allow the sample size calculation for the future RCT to be calculated. An exploration of any potential differences between the two groups in relation to the Barthel index will be completed using a *t*-test. The effect size and confidence intervals will also be calculated to inform a sample size calculation for a future definitive RCT. It is envisaged that a more complex analysis would be required to elicit an accurate description of the group differences; however, this would only be possible with a larger sample size.

The secondary outcome measures, which are the remaining outcomes at participant level, will follow the same procedure as for the primary outcome measure detailed above, as will the analysis for the only measure taken in relation to the carers (caregiver strain index). The results and appropriateness of the outcomes will be evaluated for continuation for a future RCT.

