#### Expected duration of feasibility study

Participants will be recruited over a 9-month period and followed-up for 3 months.

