## Discussion

The enhanced multidisciplinary rehabilitation programme has been developed from programme theories obtained from a realist review of the hip fracture rehabilitation literature, with contributions from a survey of current practice and focus groups of patients, carers and rehabilitation team members. In this randomised feasibility study, we will use mixed methods to examine different aspects of this programme: its acceptability in focus groups; quality of life, functional ability, mental health, potential psychological mediators of outcome and health service use with patient completed outcome measures; objective measures of physical function; patients’ preference for the content of the programme in a discrete choice experiment; routinely collected information to measure health service use and process outcomes; and adverse event reporting. The criteria for judging the feasibility of a future RCT will be an eligibility rate of greater than 50% of those screened (lower bound of a 95% confidence interval (CI) would be 44%), recruitment rate greater than 25% of those eligible (lower bound of a 95% CI would be 18%), retention rate at 3-month follow-up greater than 75% (lower bound of a 95% CI would be 63%).

Phase II studies are primarily intended to test the feasibility and acceptability of the various trial methods prior to a larger definitive phase III randomised controlled trial. However, they also provide an opportunity to compare and contrast different methods such as patient-completed questionnaires with objective measures of physical function; collecting health resource data from routinely collected information with patients’ self-report; different process and outcome measures for self-efficacy, functional ability and quality of life; and different objective measures of physical function.

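### The percentage of recruits over the cohort can set 9 months of recruitment against 6 months of admissions, and the eligibility criterion has two denominators and an ineligibility reason that the entry criteria do not contain

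*Protocol article*

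**What the plan says.** All references are to the protocol article.

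- **Cohort window.** Selection of subjects for cohort study takes patients aged 65 and over admitted to the three hospitals "with hip fracture during the first 6 months of the study period". It expects 100 to 180 "admitted to each of these hospitals (a total of 300 to 540) in a 6-month period".
- **Trial window, first statement.** Selection of subjects for randomised feasibility study expects to identify and "invite 150 patients (50% of a conservative estimate of the total") "during the 6-month study period to participate in the embedded feasibility study". The recruitment target is 50.
- **Trial window, second statement.** Expected duration of feasibility study says: "Participants will be recruited over a 9-month period and followed-up for 3 months".
- **Recruits over cohort.** Under Statistical analysis, the number of eligible patients recruited "will be expressed as a percentage of the numbers in the cohort data set", and also as a percentage of those found eligible in the feasibility study. The section on routinely collected data gives the same cohort percentage. Neither place limits the numerator to the cohort's months.
- **Rules with thresholds.** Statistical analysis sets eligibility at 50% of cohort patients (minimum 44%), recruitment at 25% of eligible patients (minimum 18%) and retention at 75% (minimum 63%). The Discussion restates the first as an "eligibility rate of greater than 50% of those screened", with the same 44%.
- **Ineligibility reasons.** The list in Statistical analysis includes age and "living within the study area but outside the area where the intervention could be delivered". The inclusion criteria require living and receiving NHS rehabilitation within the health board's area. Neither they nor the exclusion criteria mention a delivery area.

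**The concern.** Recruitment and retention figures are the main outcomes of this feasibility study, so each rate needs a numerator and a denominator drawn from the same patients over the same months. Recruits over cohort does not meet that test if recruitment runs for 9 months: the numerator gains patients from months 7 to 9 while the denominator stops at month 6. This is the figure that turns hospital admissions into expected recruits, so a future trial's sites and duration could be planned on it.

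The eligibility rate has a different problem. Patients in the cohort and patients screened on the wards need not be the same group. Age as a reason for ineligibility can arise among screened patients but not in a cohort already limited to 65 and over. The delivery-area reason also leaves it open whether such patients count as eligible, and that count enters two of the three threshold rules.

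**Working it through.** **Inputs.** Cohort window 6 months; trial window 6 or 9 months; admissions 300 to 540 per 6 months; 150 invited (50% of 300); target 50 recruits. Assumption: constant monthly admissions.

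**1. Reproduce the stated minimums.** The formula is the Wald limit p − 1.96 × √(p(1 − p)/n). The article does not print n; the values below are inferred from its own counts.

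| Rule | p | n | Lower limit | Stated |
|---|---|---|---|---|
| Eligibility | 0.50 | 300 | 44.3% | 44% |
| Recruitment | 0.25 | 150 | 18.1% | 18% |
| Retention | 0.75 | 50 | 63.0% | 63% |

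All three reproduce. The first two match 6-month counts. With 9-month counts (300 × 9/6 = 450 and 150 × 9/6 = 225) they would be 45.4% and 19.3%.

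**2. Recruits over cohort.** With 9 months of recruitment, the matched denominator is 9 months of admissions.

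| Admission rate | 50 / 6-month cohort | 50 / 9 months of admissions | Ratio |
|---|---|---|---|
| Conservative | 50/300 = 16.7% | 50/450 = 11.1% | 1.5 |
| Upper | 50/540 = 9.3% | 50/810 = 6.2% | 1.5 |

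Cutting the numerator instead gives the same answer: at a steady rate, 50 × 6/9 = 33.3 recruits fall in the cohort's months, and 33.3/300 = 11.1%.

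**3. Which window is operative?** At 25% recruitment, 150 patients yield 37.5 recruits, short of 50. Over 9 months, 225 yield 56.25. The target therefore fits 9 months better, but this is an indication and not proof.

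**4. Does the mismatch reach the threshold rules?**

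- *Recruitment (25%/18%).* The rule concerns eligible patients, and Statistical analysis offers those identified as eligible in the feasibility study as denominator. Over 9 months that is 50/225 = 22.2%, with matched windows. Only a 6-month count of eligible patients would inflate it (50/150 = 33.3%).
- *Eligibility (50%/44%).* The rule is worded as a share of cohort patients, and Cohort study outcomes counts within the cohort those who meet the inclusion criteria. That is 6 months over 6 months. Only setting 9 months of eligible patients against the 6-month cohort would make 33.3% read as 50% (0.50/1.5) or 29.3% read as 44% (0.44/1.5).
- *Retention (75%/63%).* The cohort does not enter.

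**5. Delivery-area reason.** Let N be the cohort, R the recruits, E the eligible patients without those outside the delivery area, and d the patients outside it who meet every listed entry criterion. Counting d as ineligible changes eligibility from (E + d)/N to E/N, which is lower, and recruitment from R/(E + d) to R/E, which is higher. The article gives no figure for d, so only the directions can be stated. They hold for either window.

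**The case against.** The strongest reply is that nothing decisive turns on the mismatched percentage. Recruits over cohort has no cut-off, and the same sentence supplies a second denominator whose window matches. The eligibility rule is a subset of the cohort by its own wording. The stated 44% and 18% fit 6-month counts, which suggests that the criteria were conceived on matched windows. If the 6-month window governs the trial as well, the factor of 1.5 disappears. The Discussion sentence is a short summary with the same 50% and 44%. Age is a proper entry in a screening log because it is an inclusion criterion. The delivery-area reason lowers the eligibility rate, so it does not add to any overstatement there.

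Most of this stands. A reader might infer that the go/no-go rates themselves are inflated by half. The article does not support that: it would require the analyst to mix windows, which the text does not rule out but does not ask for either. The change from cohort to screened patients does not create the 1.5 factor.

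Three things are left. The two window statements cannot both be right. The recruits-over-cohort percentage follows the text into a mismatch if 9 months is operative. And being a summary does not settle which eligibility denominator applies, nor does the direction of the delivery-area effect settle who is eligible, since the same reclassification raises the recruitment rate.

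**Conclusion.** The concern holds in a limited form.

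- The 6-month and 9-month statements contradict each other. If 9 months is operative, recruits over cohort is overstated by up to 1.5: 16.7% instead of 11.1% for 50 recruits at the conservative admission rate, or 9.3% instead of 6.2% at the upper rate. This assumes steady admissions and no limit on the numerator's months. If 6 months is operative, there is no overstatement.
- That percentage is a main outcome without a threshold. The recruitment and retention rules are not inflated when the denominators in Statistical analysis are used. The eligibility rule is inflated only if eligible patients from months 7 to 9 are set against the 6-month cohort.
- Independently of the window, the eligibility criterion has two denominators, and the delivery-area reason shifts the numerator of the 50% rule and the denominator of the 25% rule. The size of either effect cannot be derived from the article.

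**What to change.** 1. Reconcile Selection of subjects for randomised feasibility study with Expected duration of feasibility study, so that one recruitment window is stated.
2. For every percentage with the cohort as denominator, count only patients admitted in the cohort's 6 months, and report later recruits separately.
3. Use the cohort as the eligibility denominator in both Statistical analysis and the Discussion, with the numerator taken from the same cohort months as in Cohort study outcomes.
4. Align the ineligibility reasons with the entry criteria: either add the delivery-area condition to the criteria, or count those patients as eligible but not recruited.

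The cost is some wording and a filter on admission date in the screening log. If 9 months is the operative window, the recruits-over-cohort percentage will look lower than it would otherwise.
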